#### **7.3.2 Secondary outcomes**

Adherence outcomes

1. 60% of PMC drugs (defined as administration of 6 or more [but less than 9] of the daily dosages out of the total of 9, given 2, 6 and 10 weeks after discharge
2. 30% of PMC drugs (defined as administration of 3 or more [but less than 6] of the daily dosages out of the total of 9, given 2, 6 and 10 weeks after discharge
3. <30% of PMC drugs (defined as administration of less than 3 of the daily dosages out of the total of 9, given 2, 6 and 10 weeks after discharge

Clinical safety outcomes

4. All-cause mortality
5. Incidence rate of all-cause hospital readmission

6. Incidence rate of readmissions due to severe anaemia (Hb <5g/dL) or severe malaria (parenteral quinine or artesunate)
  7. Incidence rate of non-severe all-cause sick-child clinic visits
  8. Incidence rate of clinic visit due to RDT/microscopy confirmed non-severe malaria
- Cost-effectiveness outcomes

9. Cost of delivering the PMC services (providers perspective)
10. Cost of receiving the PMC services (patients perspective)

Feasibility and acceptability outcomes

11. The acceptability of PMC
12. Adaptations to their working practices required to implement PMC
13. Perceptions of the feasibility of implementing PMC through different delivery mechanisms

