| Outcomes                            |                         |                               |                       |                                                                                                                                                                           |          |          |                      |          |          |                         |           |           |                       |
| PMC uptake                                 |                         |                               |                       | X                                                                                                                                                                         | X        | X        | X                    | X        | X        | X                       | X         | X         |                       |
| Clinic visits, Adverse events              |                         |                               |                       | Passive surveillance in clinics in the catchment area, 26 weeks from 0-26 weeks (clinical malaria and other acute illnesses) (RDT/smear, Hb, and other tests as required) |          |          |                      |          |          |                         |           |           |                       |
| Hospitalisation                            |                         |                               |                       | Passive surveillance for hospital admission in the catchment area, 26 weeks from 0-26 weeks                                                                               |          |          |                      |          |          |                         |           |           |                       |
| Vital status                               |                         |                               | X                     | X                                                                                                                                                                         |          |          |                      | X        |          |                         |           | X         | X                     |

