### **7.2 Specific objectives**

1. To compare PMC uptake (adherence) levels between community- versus health facility-based strategies
2. To determine whether SMS or Health Surveillance Assistant (HSA) reminder has additional benefit on PMC uptake (adherence) levels
3. To determine the safety of PMC delivery in the community versus in the health facility
4. To determine and compare the cost to the health service of delivering PMC using each individual delivery strategy
5. To determine and compare the cost to the patients and guardians of receiving PMC using individual delivery strategies
6. To determine the feasibility and acceptability of delivery of PMC in a typical Malawi health system setting

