## 8.3 SAMPLE SIZE

Although a factorial design will be used, only the main effects of PMC mode of delivery and the “use of SMS/HSA reminders” are of primary interest. There are five arms in total as described above such that each of the four intervention arms will be compared to the control arm (Arm 1: Mother given at discharge without SMS reminder). Each village cluster contributes 2 to 4 children/year on average with severe anaemia. Thus, the cluster sizes vary and we have accounted for this in sample size calculations in order to achieve the number of clusters that would have enough power to detect the desired difference. The sample size calculation has been adjusted in the design effect using the coefficient of variation method [11-13]. This has assumed that the cluster sizes will be uniformly distributed between 2 and 4 children i.e. U[2,4]. This gives a mean cluster size of 3 children per village per year and a standard deviation of cluster sizes of 0.58. Hence the coefficient of variation of cluster sizes (CV) is  $0.58/3 = 0.19$  and  $CV^2 = 0.036$ . Assuming an

intra-cluster correlation coefficient (ICC) of 0.1 and allowing for 10% loss-to-follow-up, a sample size of 25 clusters of an average of 3 children per village (75 children per arm, N=375 overall (for 125 clusters for the 5 arms)) has 80% power to detect a 25% absolute increase in uptake from an estimated 50% in the OPD and delivery at home groups to 75% in the arms supported by SMS reminders ( $\alpha=0.05$ ). The ICC of 0.1 is slightly more conservative than the ICC in a previous trial of delivery approaches for IPTc in the Gambia (0.08)[14].

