### 8.6.2 Drug administration

For all the OPD arms, the first dose will be given as a crushed powder mixed with water at the OPD. The remaining two doses will be given to take at home during the following two consecutive days. Participants in other study arms will take all the drugs at home. Participants will be advised to give the drug to the child at about the same time each day with water. Should a caretaker forget to give the drug dose at the set time, they will be advised to take it as soon as realised and to continue the recommended regimen until the dose is completed.

Participants who take the Eurartesim at the OPD will be observed for 60 minutes. Should a participant vomit within 30 minutes of receiving the treatment drug, the full dose will be re-administered. Should a participant vomit within 30-60 minutes of drug intake, half dose will be re-administered.

To minimise QTc prolongation, the manufacturer of Eurartesim advises patients to take the first day's dose approximately three hours after meals as fatty food can increase the absorption of piperaquine. However, overall studies show that DP is well tolerated and can be given with small amount of food, although trough drug levels are also effective when given to fasting patients.

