#### 8.9.2.2 Clinical outcomes

1. all-cause mortality
2. Incidence rate of all-cause hospital readmission
3. Incidence rate of readmissions due to severe anaemia (Hb <5g/dL) or severe malaria (parenteral quinine or artesunate)
4. Incidence rate of non-severe all-cause sick-child clinic visits
5. Incidence rate of clinic visit due to RDT/microscopy confirmed non-severe malaria

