#### **11.7.4 Data Analysis**

The % of children receiving IPTpd according to schedule will be compared by relative risks (95% CI), adjusted for prognostic factors at baseline using log binomial or Poisson regression with adjustment for cluster effects. Hazard ratios will be calculated for morbidity endpoints using Cox regression for repeated events with robust standard error estimation methods to account for correlation between episodes within children. Incidence rates per child-year and absolute rate reductions will also be calculated.

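### Safety by delivery mode is an objective, but tolerability and dosing errors are not outcomes, and such events are watched for at the OPD and not asked about at home

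*Protocol*

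**What the plan says.** - **Objective.** Protocol 7.2, objective 3: "To determine the safety of PMC delivery in the community versus in the health facility".
- **Outcomes.** Section 7.3.2 lists five items under "Clinical safety outcomes": all-cause mortality, all-cause readmission, readmission for severe anaemia or severe malaria, all-cause sick-child visits, and visits for confirmed non-severe malaria. Section 8.9.2.2 gives the same five under "Clinical outcomes".
- **Analysis.** Beyond uptake, 11.7.4 says "Hazard ratios will be calculated for morbidity endpoints using Cox regression for repeated events", plus incidence rates.
- **Adverse events.** The Outcomes block of Table 2 (section 4.2) has a row "Clinic visits, Adverse events", filled by passive surveillance. Mothers in all arms are told to report any adverse event to the hospital (8.7.6.1).
- **Dosing at the OPD.** Section 8.6.2: "For all the OPD arms, the first dose will be given as a crushed powder mixed with water at the OPD". The child is then observed there for 60 minutes. The other two doses of the course are given at home.
- **Dosing at home.** Section 8.6.3 leaves observation to the mother. She repeats the full dose after vomiting within 30 minutes and half the dose after vomiting at 30 to 60 minutes, once only.
- **Home visits.** Unannounced visits on day 4 or 5 of each course use a pill count and an interview about missed doses and their reasons (8.9.1, 8.12.4). Section 8.12.1 confines home visits to adherence, vital registration and health economics, and excludes clinical assessment.

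**The concern.** Every child receives the same drug. The modes differ in where the three courses are kept, who gives the first dose of each, and who watches the child afterwards. The harms most specific to delivery mode are therefore vomiting, repeat dosing and a wrong amount given. The protocol itself makes these relevant: 14.5.4 names dose-dependent QTc prolongation as the main safety concern with piperaquine, and 8.6.1.1 allows half and quarter tablets.

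The listed outcomes do not isolate such harms. Malaria and severe-anaemia events mainly show lack of protection. Deaths, all-cause readmissions and sick-child visits are legitimate net outcomes, but they mix harm with the benefit of better uptake.

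Followed as written, objective 3 would be answered by these net outcomes plus adverse event reports whose collection depends on the arm. The trial is meant to inform policy, so a statement that home delivery is as well tolerated as OPD delivery would have little behind it. A later analysis plan could tabulate recorded events by arm. It could not recover vomiting or dosing errors at home that nobody asked about.

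**Working it through.** No figure in the plan belongs to this point, so the check compares the sections, then counts planned doses, then asks how precise the remedy would be.

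**1. How a vomited, repeated or wrong dose can reach the record**

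| Route | Community arms | Facility arms |
|---|---|---|
| Staff give and watch the dose (8.6.2) | none | first dose of each course |
| Mother watches (8.6.3) | all doses | second and third dose of each course |
| Mother reports an adverse event (8.7.6.1) | yes | yes |
| Passive clinic surveillance (8.7.5.1, 8.12.6.1) | yes | yes |
| Day 4-5 visit (8.9.1, 8.12.1, 8.12.4) | missed doses; referral if found ill | same |
| End visit (8.12.5) | history and examination | same |

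Only the first row separates the modes. The day 4-5 visit could even this out, but its stated content does not. A pill count shows tablets gone, not whether the child kept them down. Referral catches only illness still present. At 15 weeks, the end visit falls 15 - 2 = 13, 15 - 6 = 9 and 15 - 10 = 5 weeks after the three courses are due, which is late for recalling a vomited dose.

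**2. Planned doses watched by staff**

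Inputs: 75 children per arm (8.3, "a sample size of 25 clusters of an average of 3 children per village"), three community and two facility arms (8.1), and 3 courses x 3 days = 9 doses.

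- Facility: 2 x 75 = 150 children, 150 x 9 = 1,350 doses, of which 150 x 3 = 450 are watched (3 of 9).
- Community: 3 x 75 = 225 children, 225 x 9 = 2,025 doses, of which 0 are watched.

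The 450 assumes that every OPD visit is attended.

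**3. Precision of a comparison by mode**

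Inputs from 8.3: mean cluster size 3, squared coefficient of variation 0.036, ICC 0.1, loss 10%. The ICC was chosen for uptake, and using it for adverse events is an assumption. The risks of 2% and 10% are also assumed.

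- Design effect = 1 + ((1 + 0.036) x 3 - 1) x 0.1 = 1.211.
- Children after loss: community 225 x 0.9 = 202.5; facility 150 x 0.9 = 135.
- 95% half-width = 1.96 x sqrt(p(1 - p)(1/n1 + 1/n2) x 1.211).

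| Comparison | p = 2% | p = 10% |
|---|---|---|
| All arms, 202.5 v 135 | 3.4 points | 7.2 points |
| Without the Health Surveillance Assistant (HSA) reminder arm, which has no facility counterpart, 135 v 135 | 3.7 points | 7.9 points |

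With ICC = 0 the first row becomes 3.0 and 6.5 points, so the ICC assumption matters little. At 2% the half-width exceeds the risk itself. The normal approximation is then rough, and the comparison would say little.

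**The case against.** **Serious events are covered.** A reader might infer that objective 3 has no safety outcome, or no serious-event outcome. The protocol does not support that. Death and all-cause readmission are serious events by the usual definition and are listed in 7.3.2, and Table 2 places adverse events among its outcomes. The gap is confined to non-serious or drug-related events, vomiting and redosing, and dosing errors.

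**Collection is broader than the OPD.** Mothers in all arms are told to report adverse events and bring in ill children, parents of children who discontinue are asked about adverse events (8.8), and everyone is due an end visit. Drug is packed per child by weight (8.6.4.1), which limits errors in choosing a dose, and unused drug and containers are returned and reconciled (8.6.4.4). All of this stands. It narrows the gap, but none of these routes asks every mother, soon after each course, whether the child vomited or was dosed again.

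**Much of this belongs to the analysis plan or the forms.** Adverse event tables by arm do, and their absence is no fault. The different group headings in 7.3.2 and 8.9.2.2 are cosmetic. The spot-check questionnaire is not in the document and may ask more; vomiting could also be given as a reason for a missed dose. But 8.12.1 states what the home visits are for and excludes clinical assessment. Data not collected cannot be restored at analysis.

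**No bias is demonstrated.** A reader might infer that facility delivery will look less safe by a calculable factor. That would need the chance that a home event is recorded, which the protocol does not give. It also depends on OPD attendance, in a trial that assumes 50% uptake without reminders. Neither the size nor the direction of a net bias can be stated.

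**Conclusion.** The point holds in a limited form. Objective 3 promises safety by delivery mode, and the outcomes cover serious events through deaths and readmissions. They omit tolerability and dosing errors, and the protocol fixes uneven ascertainment of these: staff watch 3 of 9 planned doses in the facility arms, if visits are attended, and 0 of 9 in the community arms. The visit common to all arms is not described as asking about them. The difference bears mainly on events soon after a dose. Deaths and readmissions are little affected. The conclusion rests on 8.9.1 and 8.12.1 describing the home visit fully; if the questionnaire already asks about vomiting and adverse events in all arms, only the text needs correcting. This is a cheap improvement of low to moderate priority and does not threaten the primary comparison.

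**What to change.** - Amend 8.9.1 and 8.12.1 so that the day 4-5 spot check in every arm asks one short, identical question: since this course began, has the child vomited a dose, been given a dose again, been given a wrong dose, or had any adverse event? Define a wrong dose on the form.
- Report the proportion of children with any such event by delivery mode, per child randomised, as an estimate with a cluster-adjusted confidence interval and no test. Show the number of courses given beside it, since better uptake means more exposure.
- Report separately the events seen only during the 60-minute OPD observation.
- Keep outcomes 4 to 8 of 7.3.2 as they are.

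**Cost.** One form item, one table and a change of wording. If the spot checks cover all children, as 8.9.1 and 8.12.4 read, the 375 x 3 = 1,125 visits are already planned. Section 8.12.1 speaks of visiting only some of the children. If that governs, up to 3 visits are added for each child outside that group, though the primary outcome needs them anyway. Intervals will be wide (about 3 to 8 points), and differences in reporting due to the open-label design will remain.

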## 8 DESIGN AND METHODOLOGY

### 8.1 Trial Design

This is a single-centre, matched, cluster randomized, 5-arm, factorial design trial comparing the uptake of PMC-DHP delivered through health facility or community-based approaches with or without SMS/HSA reminders. All children will receive DHP and hence there are no placebo arms in this trial. However, children shall be randomized to receive PMC as follows:

- a. *Community-based*: Mother given **all** PMC drugs at discharge without an SMS reminder
- b. *Community-based*: Mother given **all** PMC drugs at discharge with an SMS reminder
- c. *Community-based*: Mother given **all** PMC drugs at discharge with HSA reminder
- d. *Facility-based*: Mother asked to return to outpatient departments (OPD) for each **monthly** PMC without an SMS reminder
- e. *Facility-based*: Mother asked to return to outpatient departments (OPD) for each **monthly** PMC with an SMS reminder

Where;

**Arm 1: Mother given at discharge without SMS reminder:** At discharge, the OPD staff will give the mother or guardian all drugs for PMC-1, PMC-2 and PMC-3 and instruct mother/guardian when to give these drugs.

**Arm 2: Mother given at discharge + SMS reminder:** At discharge, the OPD staff will give the mother or guardian all drugs for PMC-1, PMC-2 and PMC-3 and instruct mother/guardian when to give these drugs. Additionally they will be reminded via SMS to give the drugs to the child a date before each treatment course is due.

**Arm 3: Mother given at discharge + HSA reminder:** At discharge, the OPD staff will give the mother or guardian all drugs for PMC-1, PMC-2 and PMC-3 and instruct mother/guardian when to give these drugs. Additionally HSA or Village Health Volunteers (VHV) which are part of existing networks of community based volunteers taking part in village health committees will be reminded via SMS to go and remind the mother to give the drugs to the child a date before each treatment course is due.

**Arm 4: Mother given monthly at OPD without SMS reminder:** At discharge, the mother will be requested to return to the OPD to collect drugs for PMC-1, PMC-2 and PMC-3.

**Arm 5: Mother given monthly at OPD + SMS reminder:** At discharge, the mother will be requested to return to the OPD to collect drugs for PMC-1, PMC-2 and PMC-3. Additionally they will be reminded via SMS to come to the clinic to collect drugs a date before each treatment course is due.

#### 8.1.1 Rationale for the trial arms

There is need to assess a number of strategies for effective delivery of PMC in a largely rural community that would typically benefit from this intervention. Presently in African health systems and particularly Malawi there is no post-discharge health management system. Most patients once discharged are no longer expected to have contact with the health system apart from for EPI visits (if less than 9 months old). Post-discharge health care becomes very important in severe anaemia as it has been shown that they are at particular risk of dying or having another episode of severe anaemia.

We postulate that this post-discharge care in the form of PMC may be delivered either in the community or at a health facility. The most likely scenario where the health care provider is least involved would be where mothers are given PMC drugs on discharge from hospital and allowed to administer the drugs on her own to the child ([Arm 1](#)). However as we postulate that the mother could forget to administer the PMC, we would like to test a number of reminder systems. The first is through the use of SMS technology, which has been shown to be user friendly and acceptable from our own pilot work and other programs in Malawi that are currently using it ([Arm 2](#)). FrontlineSMS™ is a simple and free desktop software that enables instantaneous 2-way communication to any mobile handset. It is easy to implement, simple to operate and the only cost is for the sms that is sent ([www.frontlinesms.com](http://www.frontlinesms.com)).

An alternate reminder system is the use of HSA. HSA are Ministry of Health (MoH) employees who are responsible for basic health promotion activities in the community. Ideally MoH strives to have 1 HSA for every 1000 people, but in reality they often cater for much larger populations. As they are the main MoH community health workers they are usually over burdened with many disease control programs. In some areas in rural Malawi there are Village Health committees, which are made up of voluntary members of the community. They work hand in hand with the HSA. We postulate that HSAs and where available village health volunteers (VHVs) are an option for reminding mothers to give PMC to their child ([Arm 3](#)).

Alternative delivery strategies for PMC are to have the mother return to the health care facility to receive drugs for each treatment course. This is a plausible strategy as this occurs in many chronic illness cases where drugs are supposed to be collected from a health facility (e.g. in TB, HIV). In recent years there has been successful disease control programs operationalizing more decentralised drug delivery programs in the community. In this trial the mother may be reminded to come collect their child's PMC drugs using SMS ([Arm 4](#)) or not ([Arm 5](#)).

#### Figure 1: Study Arms

|                         |                               | Mode of Reminder |         |                           |
|-------------------------|-------------------------------|------------------|---------|---------------------------|
|                         |                               | No SMS           | SMS     | HSA Reminder  |
| Mode of delivery of PMC | All at Discharge  | Group 1          | Group 2 | Group 3                   |
|                         | Monthly at OPD    | Group 4          | Group 5 |                           |

Mothers given all PMC treatment courses at discharge

Mothers return to OPD for each PMC treatment course

HSA is requested to remind mother for each PMC treatment course at home

### 8.1.2 Sub-studies

The cost of delivering the intervention from the providers perspective and the cost of receiving the intervention from the patients perspective will be assessed through a Economic evaluation sub study involving a sub set of patients participating in the main malaria chemoprevention post-discharge delivery mechanisms trial.

A health services qualitative study will be conducted on a subset of participants in the main delivery mechanisms trial who will be enrolled towards the end in order to assess the level of acceptability of PMC; adaptations to health workers working practices to implement the intervention; perceptions of the feasibility of implementing PMC through different delivery mechanisms and come up with a list of recommendations on effective implementation.

